# Effects of intermittent fasting on quality of life tolerance of chemotherapy in patients with gynecological cancers: study protocol of a randomized-controlled multi-center trial

**DOI:** 10.3389/fonc.2023.1222573

**Published:** 2023-07-19

**Keywords:** intermittent fasting, quality of life, fatigue, gynecological cancers, chemotherapy

## Abstract

**Trial Registration:**

https://drks.de, identifier DRKS00031429.

## Introduction

In the 20^th^ century, researchers found that caloric restrictions prolonged the life span of rodents and reduced age-related diseases (1). Since then, therapeutic fasting has become popular in multiple medical disciplines and its positive effects on health have been documented in many preclinical and clinical trials (2). Among others, intermittent fasting (IF) as a form of time-restricted feeding has demonstrated its capability to reduce insulin resistance (3), oxidative stress and systemic inflammation (4, 5) as well as to increase neuronal stress resistance (6). Despite or maybe due to its wide establishment in the fitness and medical community, the term IF is often mistakenly used interchangeably with short-term fasting (STF) or periodic-fasting. It is characterized by a recurring switch between fasting periods (0-calory or subtotal calory intake) and eating periods (often no caloric limit or specific food restrictions). The lack of a commonly accepted definition to differentiate between the wide variety of fasting regiments needs to be kept in mind, when addressing therapeutic fasting. In a current paper, Longo et al. define IF as “an eating pattern in which short periods of fasting (16 to 48 hours) and eating periods (8 to 12 hours) are alternated” (7). In line with this definition, in our trial we define IF as a period of total calory restriction of at least 16 hours, followed by an average eating period of 8 hours, during which food intake is allowed (16:8h-IF). In contrast to this, STF or periodic fasting are often associated with longer fasting periods of around 60-72h up to multiple days (7, 8).

Besides its quantitatively measurable long-term health benefits, 16:8h-IF has recently been shown to improve quality of life (QoL) and especially the domain of fatigue in a generally healthy study population (9). These results are of great importance not only for mainly healthy people suffering from psychological or physical stress for instance due to shift work, but also for patients with cancer undergoing anti-neoplastic therapies. Especially chemotherapy (CHT) is often associated with a drastic reduction in QoL and increased fatigue, with around 62% of patients suffering from fatigue during treatment (10) and about one third still suffering from it half a year later (11). While some side effects of CHT can be sufficiently treated with modern drugs (e.g. antiemetics, analgesics), there is still a tremendous lack of treatment options for chemotherapy-induced side effects including fatigue (12). Recently, STF has shown to increase QoL and tolerance to CHT in 34 patients with ovarian and breast cancer (13) and the results of a randomized-clinical multi-center trial on STF during CHT are eagerly awaited (8). In contrast, in the DIRECT trial, de Groot et al. found no effect for a fasting-mimicking diet on QoL during CHT in 131 women with breast cancer compared to a regular diet. However, it has to be noted that solely 20% of patients in the fasting-mimicking diet group completed the trial according to the protocol guidelines. The authors report a dislike of distinct components of the fasting-mimicking diet, perhaps induced by the CHT as the main reason for non-compliance and premature discontinuations in the intervention group (14).

IF could be a promising alternative to fasting-mimicking diets, due to its non-calory restrictive and non-ingredient restrictive eating period, which offers freedom in food choice to all patients. The everyday compatibility of IF has demonstrated a high compliance of 90% in a trial conducted by our group (9).

In preclinical trials, fasting has furthermore shown synergistic antitumor activity with antineoplastic therapies (15–17). Partly, this effect is thought to be due to the reduced levels of insulin-like growth factor-1 (IGF-1) concentrations during fasting, which led to a downregulation of the mTOR, RAS and AKT pathways and consequently to an increased autophagy of healthy cells and a shifting of the energy resources towards cell repair and protection mechanisms (17–19). Cancer cells however often lack these regulatory mechanisms. This protection of healthy cells but not cancer cells against stressors including CHT has been described as “differential stress resistance” (18, 20) and might play an important role in reducing chemotherapy-induced side effects and dose-limiting toxicities, which in turn can lead to an improved QoL as well as a reduced number of treatment terminations. In line with preclinical studies, IF and STF have been shown to decrease IGF-1 levels significantly in a healthy population (9) as well as in cancer patients (14, 21). Furthermore, Vernieri et al. recently demonstrated a favorable shift of peripheral blood cells towards enhanced intratumor Th1/cytotoxic cells and activation of antitumor immune programs through a fasting-mimicking diet in breast cancer patients (21).

Despite the great potential of therapeutic fasting in oncology and its safety proven in several small clinical trials, only a few phase II/III studies have been conducted so far, none using a 16:8h-IF regiment. Thus, in this multi-center, randomized-controlled trial we aim to assess the effects of 16:8h-IF on quality of life and especially on fatigue during chemotherapy in patients with gynecological cancers.

## Methods

### Study design and setting

This study is designed as a prospective, two-arm parallel-group, multi-center, open-label, randomized-controlled clinical trial (phase III trial). It will be conducted at the Department of Gynecology and Obstetrics of the University Medical Centre of the Johannes Gutenberg University Mainz, Germany, as well as the department of Gynecology and Obstetrics at the St. Josef’s Hospital, Wiesbaden, Germany. All data will be recorded pseudonymized. Only the principle investigator of the study, as well as the study nurses in charge will have access to the pseudonymization list in case of adverse events or trial termination.

The active fasting period will be conducted for three months during CHT. Participants will be scheduled for study visits during their routine care (d1 of each cycle) and routine laboratory visits on days 8 (and 15 in three week cycles) of each cycle during the three months of the active trial period. Additional study visits will be scheduled for nutritional counseling prior to the start of the chemotherapy as well as a follow up visit at six months (**Table 1**). QoL including fatigue assessment will be performed at baseline, each week during the 12 weeks active trial period as well as at the six months follow-up. Specific quality of life aspects regarding sleep quality and pelvic floor function will only be assessed at baseline, after three months and after six months.

**Table 1 T1:** Visit overview and outcome measures assessed during each study visit.

Timepoint	Study period						
	t_-1_ *(3d - 4w prior to CHT)*	All cycles d_1_	All cycles d8	3-week cycles day 15	12 weeks after Start CHT ( ± 1 week)	Post surgery where applicable	6 months follow up ( ± 2 weeks)
Enrolment Eligibility screen Informed consent Randomization Allocation	XXXX						
Interventions Intermittent fasting Normal diet Nutritional counselling	XXX				→ →		Voluntary continuation of IFSwitch to IF possible
Assessments Demographics Medical history Current medication Anthropometric measurements Vital signs Physical examination CTCAE Hematogram Glucose/ketone levels Organ Blood panely-H2AX DNA damage essayImmunological responseTumor response Tumor markers Pathological response Radiological response	XXXXXXXXXXX(X)^3^	XXXXXXXXX^1^	XX^2^	X	XXXXXXXXX(X)	X	XXXXXXXX(X)
Questionnaires *Fatigue → FACIT-FS©General QoL → FACT-G© General wellbeing → EORTC QLQ-C30© TOI mental health TOI physical healthTumor specific FACT-B© FACT-O© FACT-Cx© FACT-En©Pelvic floor functionalitySleeping qualityAdherence diary Continuation/Acceptance/ Difficulties		XXXXXXXXXX^4^X^5^X^6^	XXXXXXXXX	XXXXXXXXX	XXXXXXXXXXXX →		XXXXXXXXXXX

* Some questionnaires can be calculated as subgroups from other questionnaires. Thus, only 2-3 questionnaires will need to be completed by the participants.

^1^ y-H2AX DNA damage essay will only be performed on the day of chemotherapy at cycle 1 day 1, after 6 weeks and after 12 weeks.

^2^ The immunological response will only be assessed at baseline (day of enrollment), as well as one week after chemotherapy is given at three time points (week 1, week 7 and week 13).

^3^ Radiological response will only be assessed in patients treated neoadjuvantly for ovarian/peritoneal or cancer of the fallopian tubes (response rate to neoadjuvant CHT), as well as in metastasized patients of all included tumor types.

^4^ Pelvic floor functionality will only be checked on day 1 of cycle 1; 12 weeks after the start of chemotherapy and during the 6 month follow-up.

^5^ Sleeping quality will only be checked on day 1 of cycle 1; 12 weeks after the start of chemotherapy and during the 6 month follow-up.

^6^ Adherence will only be checked via a daily diary in the intermittent fasting group.

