### Recruitment and randomization

Patients will be recruited at the time of diagnosis and discussion of the treatment plan after the interdisciplinary tumor conferences of each hospital had finalized the treatment schedule. Written informed consent will be obtained from all participants prior to randomization and baseline visit. Patients can withdraw consent and effectively withdraw their trial participation at any point without any disadvantages. A screening checklist including all inclusion and exclusion criteria will be assessed by a medical doctor prior to randomization. Variable block randomization stratified by tumor entities and study site will be used to randomly assign participants to intervention or control group (1:1). Block length will be disclosed upon completion of the trial. The preparation of the randomization lists will be performed by a statistically trained researcher not involved in the recruitment, allocation, or assessment of the participants. Randomization lists will be uploaded in RedCap and cannot be viewed or changed during the trial. Group allocation will be performed over the RedCap database. Patients will be allocated after obtaining consent and completing baseline assessments to confirm eligibility.

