#### Intermittent fasting group

To increase the feasibility of IF during CHT, the intervention group will be asked to follow an IF schedule of at least 16 h continuous fasting per day on a minimum of five days per week. This allows a disruption of the fasting due to chemotherapy-related issues or to accommodate everyday events such as birthdays or short visits in the IF schedule. We have successfully tested this fasting routine in a pilot study of healthy volunteers, where ketone bodies reached the desired concentration after 16 hours of fasting. We found IF to be safe and effective in reducing fatigue and increasing QoL even in healthy volunteers. The IF schedule was feasible in a stressful work environment and variable working hours during shift work (9). To ensure the positive benefits during the administration of CHT, participants will be required to adhere strictly to the 16h fasting period per day from two days before until one day after the administration of i.v. CHT. To prevent possible negative effects from reversing the metabolic switch to an anabolic state once eating again, no food intake will be allowed on the day of CHT. On the remaining time period of the cycle, the two days of non-fasting per week are allowed. The 16-hour continuous fasting interval can be started at any time point each day. While adhering to the same fasting schedule each day is recommended (e.g., fasting in the morning) to establish behavioral manners, this is not compulsory. Non-sugary drinks including water, tea or coffee without milk (soy milk, oat milk, cow milk etc.), as well as clear vegetable broth are allowed during the 16h fasting period. Within the non-fasting period of 8 hours per day no dietary restrictions will be given. However, a normo-caloric Mediterranean diet are recommended for all patients. Participants of the intervention group will receive a 20-minutes one-on-one counselling by a licensed dietician.

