### Outcome measures

#### Primary outcome

Primary outcome of this study is the difference of the mean change in fatigue from baseline to last follow-up time point of the active trial period (3 months) between the IF group and the control group. A variation of up to ± 1 week for trial termination is allowed due to potential delays of CHT (e.g. due to insufficient blood values or public holidays).

Fatigue is measured after each chemotherapy treatment using the Functional Assessment of Chronic Illness Therapy-Fatigue Scale (FACIT- FS©). This questionnaire assesses cancer therapy related fatigue. It is part of the FACIT-F© questionnaire (22) which is a combination of the Functional Assessment of Cancer Therapy general core questionnaire (FACT-G©) and the FACIT-FS©. The FACIT-FS© includes 13 fatigue related questions, which are rated on a 5-point Likert scale (not at all to very much) over the last 7 days. Scores will be calculated according to published scoring algorithms.

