Generally, the feasibility of fasting schedules is of great importance to the success of any dietary change. While IF is thought to be a very feasible diet in everyday life, especially the first 2 weeks can be challenging and are often associated with side effects such as headache and increased fatigue or thoughts about food. These changes were also seen in our pilot trial (9). However, all probands described improvements after only a few days and thoughts about the fasting process itself decreased within the trial period. Overall, the feasibility of the fasting schedule was described as high, which was also shown in the good adherence throughout the trial. However, patients receiving CHT are challenged with other obstacles such as side effects of CHT. Thus, especially in the beginning it is expected to be harder for the intervention group to stick to the proposed fasting schedule. Nevertheless, due to the flexibility of the proposed fasting schedule with possible adjustment to each patients personal preferences (fasting periods can be chosen freely and changed throughout the trial) and allowed days of the fasting regimen (e.g. for birthdays or other important life events) we expect the fasting intervention to be manageable for 12 weeks. To support patients during the initial transition to IF, the expected side effects of IF and CHT are discussed in the personal counselling with a licensed dietician, along with possible methods to counteract them while practicing IF. Furthermore, individual guidance to determine the most feasible fasting schedule depending on the patients preferences is provided during the dietary counselling and medical personal is available to support patients experiencing difficulties with the IF schedule throughout the trial.

Fatigue is a common side effect of many CHTs. In a cross-sectional study of breast cancer patients clinically meaningful fatigue was seen in almost 50% of patients under CHT (43). Unfortunately, so far fatigue cannot be treated effectively with medication and only few measures such as physical activity are known to positively influence chemotherapy-associated fatigue (44, 45). Thus, it is of utmost importance to evaluate potential treatment options to reduce fatigue during CHT, without impairment of the oncologic treatment. With demonstrated positive effects on fatigue through IF in healthy patients (9), we aim to confirm the hypothesis that IF following can decrease fatigue during CHT.

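### Table 1 schedules no fatigue score before allocation, which conflicts with the randomisation section and leaves the baseline of the primary endpoint open to exposure to the intervention

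*Protocol article*

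**What the plan says.** The primary outcome is the "difference of the mean change in fatigue from baseline to last follow-up time point of the active trial period (3 months") between the two arms. FACIT-FS items are "rated on a 5-point Likert scale (not at all to very much) over the last 7 days". The trial is open-label.

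The protocol article speaks to the timing of the baseline score in several places:

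- **Table 1, upper rows.** The t-1 visit, 3 days to 4 weeks before chemotherapy, carries the marks for eligibility, consent, randomisation, allocation and the interventions.
- **Table 1, questionnaire row.** The t-1 cell is empty. The first marks are under day 1 of the cycles.
- **Table 1, footnotes 4 and 5.** "Pelvic floor functionality will only be checked on day 1 of cycle 1; 12 weeks after the start of chemotherapy" and at six months; footnote 5 says the same of sleep quality.
- **Study design and setting.** Sleep quality and "pelvic floor function will only be assessed at baseline, after three months and after six months". Fatigue is assessed at baseline and then weekly, with no date given for baseline.
- **Recruitment and randomization.** "Patients will be allocated after obtaining consent and completing baseline assessments to confirm eligibility".
- **Baseline characteristics.** Questionnaires are completed once the patient has been recruited, with a reference back to Table 1.
- **Table 1, footnote 2.** For the immunological measurements, baseline is glossed as the enrolment day.
- **Primary outcome.** "Fatigue is measured after each chemotherapy treatment using the Functional Assessment of Chronic Illness Therapy-Fatigue Scale".
- **Intermittent fasting group.** In this arm "participants will be required to adhere strictly to the 16h fasting period per day from two days before until one day after" each intravenous administration, with no food on the chemotherapy day itself.

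**The concern.** A change-from-baseline endpoint needs a baseline that randomisation protects, that is, one taken before the patient knows her arm and before the intervention starts. The visit schedule does not provide one for fatigue. By cycle 1 day 1 a patient in the fasting arm knows her allocation and should already have fasted for two days, and the questionnaire asks about the preceding week. Her score may carry an early effect of fasting, of expectation, or of both. The control arm has no such fasting exposure, though its patients also know their allocation.

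Any arm difference already present at that visit is subtracted from the 12-week difference, and the result no longer estimates the effect of three months of fasting. No analysis can recover a pre-allocation score that was never collected, so this cannot be left to the analysis plan.

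**Working it through.** **1. Is the empty t-1 cell real?** The table has been flattened, so this was checked. The first filled cell of the questionnaire row holds twelve marks, of which the 10th, 11th and 12th carry footnotes 4, 5 and 6. In the list of instruments, the 10th, 11th and 12th are pelvic floor, sleep and the adherence diary, which are the subjects of those footnotes. The cell is therefore aligned with the list, and its first mark belongs to FACIT-FS. Footnotes 4 and 5 date their marks to day 1 of cycle 1, which identifies the column as day 1. The t-1 cell before it is empty.

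**2. What does baseline mean for questionnaires?** The design section calls the first pelvic floor and sleep assessment baseline, and footnotes 4 and 5 date it to cycle 1 day 1. FACIT-FS is first marked in the same column. For fatigue this is an inference from the schedule, not a direct statement.

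**3. Where the text differs.** The randomisation section puts baseline assessments before allocation, but ties them to confirming eligibility, and FACIT-FS is not an eligibility criterion in Table 2. The baseline section does not say whether questionnaires come before or after allocation. Footnote 2 uses a different baseline day. The primary outcome section, read literally, supplies no pre-treatment score at all.

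**4. Exposure under Table 1.** Required fasting begins two days before chemotherapy and recall covers 7 days, so at least 2 of the 7 recalled days are fasting days in the intervention arm, plus the day itself without food. If fasting starts at t-1, where Table 1 marks the interventions, the share is larger.

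**5. The plan's own figure.** Inputs from the sample size section: difference 9.1, SD 13.7, two-sided α 0.05, power 90%.

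n per arm = 2 × [13.7 × (1.960 + 1.282) / 9.1]² = 47.6, so 48. The plan's figure reproduces. Power at 48 per arm is 90.2% by the normal approximation and 89.6% by the exact t-test. The step to 55 implies 1 − 48/55 = 12.7% drop-out.

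**6. Illustration.** Orient scores so that higher is better. Let τ12 be the effect at 12 weeks and τ0 the effect already present in the cycle 1 day 1 score. The raw change-score contrast estimates τ12 − τ0. Its standard error is 13.7 × √(2/48) = 2.80. The documents give no τ0, so the shifts below are assumptions.

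| Assumed shift in fasting arm | Early worsening, true effect zero: two-sided type I error (t-test) | Early improvement, true effect 9.1: contrast left | Power (normal / t-test) |
|---|---|---|---|
| 1 point | 6.4% | 8.1 | 82.5% / 81.8% |
| 2 points | 10.9% | 7.1 | 71.9% / 71.0% |
| 3 points | 18.6% | 6.1 | 58.8% / 57.9% |

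These shifts are 11%, 22% and 33% of the 9.1-point target (1/9.1, 2/9.1, 3/9.1).

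**7. With baseline adjustment.** If the baseline enters as a covariate with slope β between 0 and 1, the contrast estimates τ12 − βτ0. The distortion shrinks but disappears only if β or τ0 is zero.

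**The case against.** The best case for the plan is that the randomisation section already requires baseline assessments before allocation. Fatigue at baseline, listed apart from the weekly assessments, can be read as a separate earlier measurement, and footnote 2 dates baseline to enrolment. The footnotes that date a questionnaire to cycle 1 day 1 concern pelvic floor and sleep, not fatigue. This much stands: the documents contradict one another, and they do not settle on a post-allocation baseline. It does not remove the point, because the schedule is what sites work from and it has no fatigue score at t-1.

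A reader might go further and infer that fasting has already altered the baseline, and that the error must favour fasting because the Discussion says "especially the first 2 weeks can be challenging and are often associated with side effects such as headache and increased fatigue". The documents do not support that. They show exposure, not an effect on FACIT-FS. The same part of the Discussion reports that pilot participants improved within a few days, and that pilot enrolled healthy volunteers, not patients about to start chemotherapy. Early improvement or positive expectation would bias against fasting. The fasting clearly required before cycle 1 is also short: the design section places the active fasting period during chemotherapy, so an earlier start from t-1 is uncertain.

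It is also fair to object that a point-for-point carry-over holds only for a raw two-time-point change score. The planned analysis is a mixed model whose handling of baseline the article does not describe.

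**Conclusion.** The point holds as a contradiction between schedule and text that affects the primary endpoint. Table 1 provides no FACIT-FS before allocation, while the randomisation section implies that baseline measurements precede it. If Table 1 is followed, the baseline is exposed to knowledge of the arm in both groups and to fasting in one. That the baseline is in fact altered, that the bias favours fasting, or that it equals the early shift in full goes beyond the documents.

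Sign and size of any bias are unknown. The range in the working rests on assumed shifts of 1 to 3 points, an SD of 13.7, 48 analysed per arm and a raw change score. Within it, type I error could reach about 19% or power could fall to about 59%. No figure in the sample size section is wrong on this account. The matter should be settled because the primary endpoint depends on it and a missing pre-allocation score cannot be supplied later.

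**What to change.** - Add FACIT-FS and the FACT questionnaires to the t-1 column of Table 1, completed after consent and before randomisation. Making their completion a condition of the allocation step in the database would enforce the order.
- State in the primary outcome section that this t-1 score is the baseline for the primary endpoint.
- Keep cycle 1 day 1 as an assessment if wanted, but label it post-randomisation.
- Bring Table 1, including footnotes 2, 4 and 5, into line with the randomisation, baseline and primary outcome sections, so that baseline has one stated meaning for each instrument.

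The cost is schedule wording and at most one extra questionnaire set at a visit that already takes place. The planned size stays at 48 per arm, 55 with drop-out.
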